# Introduction

It is estimated that in low and middle-income countries acute malnutrition affects about 52 million children aged less than 5 years [1]. While acute malnutrition is closely associated with poverty, its prevalence and severity is often greater in conflict and disaster affected areas [2]. Acute malnutrition is a leading cause of childhood mortality, accounting for 11.5% of total deaths, and contributes significantly to the global disease burden [1, 3].

Somalia has been affected by decades of political turmoil, protracted armed conflict, and intermittent natural disasters. These factors have contributed to one of the highest global prevalences of acute child malnutrition (17.4% as of April-June 2017) [4]. Conflict has disrupted not only regional agriculture and trade, but also health services and humanitarian access, increasing food insecurity, displacement and mortality, especially during periods of crisis [5]. In 2017-2018, it is estimated that 1.2 million children in Somalia will be acutely malnourished, of which over 230,000 will be severely malnourished [4]. The group most affected by food insecurity and acute malnutrition are internally displaced persons (IDP), who often live in camps in peri-urban areas and lack access to essential services [4].

Various humanitarian interventions are commonly used for the management of acute malnutrition. Cash-based interventions (CBI) have recently gained popularity compared to conventional food-based interventions [6]. CBI aim to improve the beneficiaries’ ability to acquire food and/or other needs; and they often have additional multi-sectoral objectives, such as enabling livelihood investments and can improve health outcomes [7, 8]. Furthermore, CBI are perceived as a cost-effective nutritional intervention that improves beneficiary satisfaction, and that have a positive impact on local economies.

CBI were first implemented at scale in Somalia in 2011 to respond to the famine crisis and, given the existence of functioning markets in this context and the lack of humanitarian access to southern Somalia, were seen as an essential approach for providing food assistance [9]. However, evidence of nutritional impact of CBI in this context is lacking.

The Research on Food Assistance for Nutritional Impact-Somalia (REFANI-S) consortium conducted a trial of an emergency unconditional cash transfer (UCT) program in the Afgooye Corridor, Mogadishu, Somalia in 2016 [10]. The study found that a combined UCT, non-food item kit, and free piped water increased food security, diet diversity, and reduced negative coping strategies in recipient households. However, longitudinal community surveillance showed no evidence of the UCT reducing the incidence or prevalence of malnutrition (MUAC <12.5cm or oedema). The findings of this research were consistent with other studies of CBI and nutrition and health that indicate the variable effect of CBI on nutritional indicators.[11-15]

Nonetheless, CBI are perceived to be cost effective, improve the beneficiaries’ satisfaction and impact positively on local economies as long as they are designed and implemented appropriately in a suitable context. Therefore, more information on the use and effectiveness of CTPs in the management of health and acute malnutrition during emergencies is critical, so as to understand under what circumstances they can be effective and what additional inputs may be required.

Behaviour change communication (BCC) interventions have the potential to change behaviours and improve health and nutrition in some contexts [16-18]. Delivery of BCC via mHealth[[1]](#footnote-2) approaches have been shown to be effective although the evidence suggests that the application of behaviour change theory has been sub-optimal [19]. There is some evidence that mobile phone messaging reminders for attendance at healthcare appointments can be effective at improving attendance and reducing missed appointments [20]. A 2015 meta-analysis found that mobile phone SMS messages had a small, positive, effect on a broad range of healthy behaviours and recently the potential for mHealth interventions to impact on food choice has also been demonstrated [21-23]. mHealth intervention in low income settings is a rapidly evolving field and its use in humanitarian contexts is an emerging area of great interest and public healthpotential. Combining mHealth interventions with cash or voucher transfers to achieve health objectives is an under researched topic although studies have assessed the feasibility of the approach [24]. A 2018 review called for more rigorous evaluation of mHealth interventions targeting maternal and child health [25].

This research project will develop mHealth BCC approaches to address key infant and young child feeding (IYCF) behaviours, caring practices, WASH practices, and health seeking behaviour in an emergency affected IDP population. A mHealth BCC component, if effective, could be a cost-efficient component to add to cash transfers that reach populations in insecure/inaccessible areas, as well as populations on the move. The interventions, if effective, have a high feasibility of being scaled up in Somalia and elsewhere around the world.

Using a randomised cluster-controlled 2x2 design, this study aims to assess whether a conditional cash transfer combined with mHealth BCC audio messaging, delivered through mobile phones, can improve vaccination coverage, child dietary diversity, breastfeeding practice and thereby reduce the risk of acute malnutrition in children aged 0-59 months, living in IDP camps near Mogadishu, Somalia.

# Study Goal

To ensure more effective humanitarian interventions by strengthening the evidence base on the use of cash transfers to prevent undernutrition in contexts of protracted displacement.

# Study Objective

To assess the impact of cash transfers, delivered together with behaviour change communication and conditional upon attending child health visits, on reducing the risk of acute malnutrition among children 6-59 months.

# Primary Research Question

Can cash transfers coupled with mHealth BCC and conditional upon attending a child health visit contribute to a reduction in risk factors for acute malnutrition in children, aged 6-59 months, in a crisis context characterized by significant population displacement?

# Study Setting

The research will take place in the Afgooye Corridor, an area close to urban Mogadishu. The Afgoye Corridor contains the largest IDP settlements in Mogadishu, a result of multiple protracted crises in the country. These settlements have become a safe-haven for IDPs fleeing conflicts and disasters in the regions around Mogadishu, including Lower and Middle Shabelle, Bay and Bakool regions. The IDPs subsist almost entirely on humanitarian assistance from relief agencies and from casual labor whenever such opportunities become available.

Concern has worked in Somalia, including the urban and peri-urban areas of Mogadishu since 1986. Concern has have strong security procedures as well as good relationships with local government and community leaders that have allowed safe and continuous operation during periods of high insecurity. While we have confidence that we will be able to implement the program in the planned areas, Concern also has a high capacity to implement in other areas of Somalia as well. We are flexible to work in different areas of Mogadishu based on security. We also have an operational presence in Baidoa where we also were initially planning to implement the research. In case of serious increased insecurity in Mogadishu, the project could shifted to Baidoa. The UCL research team has been working in Somalia since 2009, and the UCL Co-Investigator/Study Coordinator has worked extensively on research projects and programs within Somalia over the past 5 years.

We consider that the research question we are seeking to answer is best addressed in a complex emergency situation with high levels of acute malnutrition, and the proposed study site provides a very useful location in which this can be done.

# Interventions

Two interventions will be tested: unconditional vs. conditional cash and behaviour change vs. no behaviour change.

## Cash Transfer Intervention

Cash will be provided to households either as an unconditional or conditional cash transfer. All groups will receive cash transfers due to ethical reasons, as all households are considered to be suffering from extreme poverty and to be highly vulnerable. Randomization will be done at the cluster (camp) level. Households living in the selected camps will be listed and registered by the Concern cash distribution team.

The cash distribution will be done electronically each month and the specified amount will be sent to the registered SIM card of the beneficiary in US$. The cash transfers will be implemented by Hormuud Telecom via their EVC Plus money transfer service.[[2]](#footnote-3) Once the beneficiaries receive the cash transfer they can then use it to purchase items electronically or exchange for physical cash at a wide range of local shops. If they experience problems with use of the cash transfer they can contact the local Hormuud Telecom office for assistance. Problems can also be reported to the Concern beneficiary help line.

Cash transfers will follow the standard amounts set by the Somalia Cash Working Group based on a percentage of the Monthly Expenditure Basket (MEB). The cash transfers will be provided for 9 months. For the first 3-6 months the transfer amount provided will be that given during a humanitarian cash transfer programme; for the following 6 months the amount provided will be aligned with that given by social safety net (welfare) programmes.

The conditional cash transfer will require households with children, aged 0-59 months, to have first attended the local health clinic where they will receive a health screening, any necessary vaccinations, deworming, and vitamin A supplementation as required; and they will be issued with a child health record card. All the study camps have similar access to local health clinics. The health clinic visit will be verified by asking for the child health record cards during registration of the household for cash transfers.

Checks of child health card will be carried out monthly during the monthly monitoring household visits by CHWs. The check will monitor whether all children in the household 0-59 months are up to date on routine vaccination, vitamin A supplementation, and deworming.

The CCT and the UCT will be the same total amount per month, with equal amounts in all arms. Figure 1 shows participant flow for those in the study arm receiving conditional cash. Those receiving unconditional cash will not be advised to visit to the health clinic prior to cash distribution (although they are fully entitled to do so if they choose to) and they will not be asked to show a health record card for their children before being registered on the cash distribution list.

Figure 1 Flow Diagram of Cash Registration System for Participants in the Conditional Cash Arm

[figure not shown]

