## Behaviour Change Communication (BCC) Intervention

All study arms will receive behaviour change communication (BCC) provided by CHW during their monthly household visits. The mHealth intervention arms will receive the additional mHealth BCC that will consist of audio messages transmitted to the recipient’s mobile phone. Provision of BCC messaging will be randomized among the groups at cluster (camp) level. The planned development strategy for the mHealth BCC messages has the following key points:

- - Messaging will be developed in collaboration with Shaqodoon and Media Inc., which are companies based in Somalia and are specialists in interactive voice response (IVR) technology and creative message development, respectively.
  - Currently, we plan to deliver 12 audio messages, with two messages focused on each of the 6 health and nutrition topics listed in Table 1 below. These topics were identified as major barriers to optimal nutrition in the REFANI research.
  - Messaging will be designed following a human centred design approach, will be culturally appropriate, and will be produced using local voice actors and musicians.
  - Message content will be tested to ensure it is compelling and effective. Different formats for message delivery will be tested, such as a 6-12 episode soap opera series, or standalone short/succinct messages.
  - The messages produced will be piloted with small groups of IDP living in the same area as the study population, and revised during several iterative rounds of development prior to general use.
  - Full consideration will be given to ensuring the messaging will be acceptable to all parties of the conflict. This will ensure that listening to the message does not put any beneficiaries at risk.

Table 1 List of Topics to be Covered in mHealth Messaging

[figure not shown]

The developed audio messages will be delivered via a server, connected to the cellular network, to the registered mobile phone/SIM card of the participants in the BBC arm of the study. Figure 3 illustrates the messaging flow and associated data capture. Cash transfers are not conditional on listening to the audio messages but information on the number of messages listened to and the duration of the listening will be recorded.

Figure 2 Flow Diagram of Audio Messaging for Participants in the BCC Arm

[figure not shown]

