# Study Design

The research will take place in 20 IDP camps in the Afgooye Corridor, which are expected to contain an average population size of 65 children (aged 0-59 mo.) per camp. A 2x2 factorial design will be used with cluster randomization. A cluster will comprise one IDP camp. The study design is illustrated below.

Table 2 Study Design Summary

|  | Unconditional  Cash Transfer | Conditional  Cash Transfer |
| --- | --- | --- |
| No mHealth BCC | 5 camps | 5 camps |
| mHealth BCC | 5 camps | 5 camps |

All households within the 20 selected IDP camps will be invited to participate in the study so it is anticipated that a total of 1,300 children will be recruited. Measurements will be taken at monthly household visits, which will be done by community health workers, and continue during the course of the intervention. Children who exceed the age of 59 mo. during the course of the study will continue to be followed until the end of the follow-up period. Any new households that arrive in the IDP camps after the household recruitment has finished will not be invited to enrol.

Participant exclusion criteria:

1. Children with a disability that prevents taking weight or height measures

2. Children with a medical condition that prevents them eating a normal diet

3. Children confined to bed due to illness

4. Children living in a household in which the mother/carer is unable to respond to questions due to a speech or hearing impairment

This study design will allow us to address 2 main hypotheses:

(1) Humanitarian cash transfer conditionality improves health service utilization, increases vaccination coverage by 20%, and reduces morbidity in children aged 6-59 months.

This hypothesis will be tested by comparing the 10 clusters receiving unconditional cash with the 10 clusters receiving conditional cash transfers.

(2) A mHealth mobile phone BCC messaging intervention, linked to cash transfers, will improve health knowledge and nutrition related behaviours in a complex emergency context.

This hypothesis will be tested by comparing the 10 clusters who receive the mHealth intervention with those that do not. We will also test the secondary hypothesis that a combined conditional cash transfers and mHealth mobile phone BCC messaging intervention reduces the risk of acute malnutrition compared to those receiving unconditional cash transfers or no mHealth intervention.

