# Sample Size Calculations

The sample size available to test for differences in vaccination coverage (hypothesis 1) was assessed using clustersampsi in Stata v14. Based on current measles vaccination coverage data, collected during the REFANI trial, we expect to see a baseline coverage of around 64%. With 10 clusters (camps) per arm and an average population of 65 children (aged 0-59 months) per cluster, and allowing for an alpha risk of 0.05, a power of 0.8, and an ICC of 0.06, we will be able to detect a minimum increase of 18 percentage points. This minimum detectable difference lies below our hypothesized effect size of 20 percentage points.

To calculate a sample size to test hypothesis 2 - the effect of mHealth messaging on health knowledge and nutrition behaviours - we assumed that there will be no interaction between the mHealth and conditionality interventions. Under this assumption we assessed the utility of the available sample size to detect a difference in children’s diet diversity score between the clusters receiving the mHealth intervention and those that won’t. Based on data from the REFANI study we expect to see a baseline child diet diversity score of 3 and a SD of 2. With 10 clusters (camps) per arm and an average population of 65 children (aged 0-59 months) per cluster, and allowing for an alpha risk of 0.05, a power of 0.8, and an ICC of 0.01, we will be able to detect a minimum increase of 0.42 in the diet diversity score. These calculations confirm that the study design is well powered to detect differences in our primary outcomes.

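### The protocol randomises 20 camps with no stated restriction beyond 5 per cell, so at its own ICC a chance baseline gap above 5 points in measles coverage between the cash arms has about a 39% probability, at an avoidable cost in precision

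*Protocol*

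**What the plan says.** The Cash Transfer Intervention section gives the unit for the cash factor: "Randomization will be done at the cluster (camp) level". The Behaviour Change Communication section does the same for the other factor: "Provision of BCC messaging will be randomized among the groups at cluster (camp) level".

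Study Design adds that "A 2x2 factorial design will be used with cluster randomization" and that "The research will take place in 20 IDP camps in the Afgooye Corridor". Table 2 sets the cell sizes; its first row reads "No mHealth BCC | 5 camps | 5 camps", and the second row has the same numbers. Hypothesis 1 is tested by "comparing the 10 clusters receiving unconditional cash with the 10 clusters receiving conditional cash transfers".

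No stratification, matching, minimisation or constraint is stated. The remark that the study camps have similar access to clinics describes the camps; it does not restrict the draw.

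For planning, "we expect to see a baseline coverage of around 64" per cent for measles, with 10 camps of 65 children per arm "and an ICC of 0.06, we will be able to detect a minimum increase of 18 percentage points".

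The Data Analysis section plans linear and logistic regression, adjusted for covariates that prove to be associated with the outcomes. It describes difference-in-difference analysis for mediating variables such as knowledge. Baseline vaccination coverage is not named in either place.

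**The concern.** With 20 units, a draw restricted only by cell size can leave the arms visibly different on the outcome that decides hypothesis 1. An ICC of 0.06 at 64% coverage means that the protocol itself expects camps to differ in true coverage by about 12 points (1 SD) before anything starts. A 5-point gap at baseline is a quarter of the hypothesised 20-point effect. Readers will ask how much of an observed difference was there at the outset, and an analysis that picks covariates by observed association answers them less convincingly than one fixed beforehand.

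The timing also matters. A later analysis plan can specify adjustment, but it cannot rebalance camps that have already been drawn.

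**Working it through.** **Inputs** (Sample Size Calculations unless noted): baseline coverage p = 0.64; ICC = 0.06; m = 65 children per camp; 10 camps per arm; alpha 0.05, taken as two-sided; power 0.8; hypothesised effect 20 points. Allocation of 5 camps per cell, hence 10 v 10 per factor, is from Study Design.

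**1. The protocol's own figure.** Design effect = 1 + 64 × 0.06 = 4.84. Effective sample per arm = 650 / 4.84 = 134.3. The minimum detectable increase from 64% is then:
- 15.3 points (pooled z);
- 16.0 points (unpooled, t on 18 df);
- 17.4 points (baseline variance in both arms, t on 18 df);
- 18.1 points (maximum variance at p = 0.5, t on 18 df);
- 19.4 points (constant between-camp coefficient of variation).

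The stated 18 is not reproduced exactly, but it is conservative against the usual formulas and nothing below depends on it. The companion figure of 0.42 for diet diversity does reproduce: design effect 1.64, effective sample 650 / 1.64 = 396.3, and (2.101 + 0.862) × 2 × √(2/396.3) = 0.421.

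**2. Size of the chance imbalance.**
- True between-camp SD = √(0.64 × 0.36 × 0.06) = 0.118.
- Observed camp SD = √(0.64 × 0.36 × (0.06 + 0.94/65)) = 0.131.
- SD of the 10-v-10 difference = 0.131 × √(1/10 + 1/10) = 0.0586, or 5.9 points.
- P(|difference| > 5 points) = 2 × (1 − Φ(0.05/0.0586)) = 0.393. A beta-binomial simulation of 20 camps gives 0.394.
- P(|difference| > 10 points) = 0.088.
- P(more than 5 points in favour of one named arm) = 0.197.

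**3. Sensitivity of the 0.393.**
- Measles coverage is defined for children aged 9 to under 59 months, so fewer than 65 per camp count. With 55 or 45 (assumed) it is 0.402 or 0.413.
- Unequal camp sizes, CV 0.3 to 0.7 (assumed): 0.41 to 0.47.
- Between-camp variation alone: 0.34.
- Other ICCs at 65 per camp: 0.14 (ICC 0.01), 0.27 (0.03), 0.49 (0.10).

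**4. Is this variance already counted?** Yes. 5.86 × (1.96 + 0.84) = 16.4 points, or 5.86 × 2.963 = 17.4 with t on 18 df. The 17.4 is the third figure in step 1: the imbalance SD and the planning standard error are the same quantity.

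**5. What a constrained draw does to the gap.** The simulation used 400 sets of 20 camps with 1,000 allocations each (5 per cell), keeping the best-balanced 10% across both factors.
- Cell sizes only: mean absolute coverage gap between the cash arms 4.7 points.
- Balancing coverage alone: 1.2 points.
- Balancing coverage and camp size with equal weight (size CV 0.5 assumed): 2.2 points, with about 5% of draws still above 5 points.

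**6. What it does to precision.** With an assumed baseline-to-endline camp correlation of 0.5, the standard error of the cash effect is about 5.9 points unadjusted, 5.2 with baseline adjustment alone, and 5.0 with constraint plus adjustment. As a check, 5.86 × √(1 − 0.5²) = 5.07. Of the 0.9-point gain, 0.7 comes from the adjustment.

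**The case against.** The strongest reply is that the protocol says nothing wrong. It gives the unit and the cell sizes and is silent on how the sequence is generated, which is compatible with a stratified or constrained draw. Simple cluster randomisation would also be valid, and the power calculation already allows for this variation. Covariate lists commonly sit in an analysis plan.

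Much of this stands. A reader might infer that the trial is biased or underpowered because of the allocation. The documents support neither: chance imbalance leaves the type I error intact, and step 4 shows that the 5.9 points are already in the planning variance, so they must not be deducted a second time from the 20-point target.

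A reader might also extend the measles figures to the mHealth factor or to single cells of 5 camps. Hypothesis 2 concerns knowledge and nutrition behaviours and was powered on diet diversity with an ICC of 0.01, and no measles comparison between single cells is planned. Nor can imbalance in exposure to the earlier cash trial be asserted: the Introduction places that trial in the same corridor but does not say that any of these 20 camps took part.

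What does not stand is deferral of the whole matter to the analysis plan. Restriction belongs to the draw. And where the protocol does speak about adjustment, it selects covariates by observed association.

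**Conclusion.** The point holds as an avoidable loss of precision and credibility, not as an error that invalidates the test. At the protocol's own inputs, the baseline measles difference between the cash arms has an SD of 5.9 points and exceeds 5 points, in either direction, with probability about 39%. This rests on applying the ICC of 0.06 to baseline coverage, which is the natural reading because it is given beside the 64%, and on taking the 5-per-cell rule as the only restriction because no other is stated.

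The size of the benefit is less certain. The gap can be cut by half or more, but how far that tightens the effect estimate depends on the baseline-to-endline camp correlation, which the protocol does not give. Most of the tightening comes from pre-specified adjustment. The change should be made before the draw; if the camps have already been allocated, only the adjustment remains available.

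**What to change.** **Allocation (Cash Transfer Intervention and Study Design).** State covariate-constrained randomisation. List all 20 camps, and record camp-level measles coverage and number of children aged 0-59 months before any camp learns its allocation. Generate allocations with 5 camps per cell, keep the best-balanced 10% on both variables across both factors, and draw one at random. If coverage cannot be had in time, balance on camp size from the listing. The order matters: households in the conditional arm attend a clinic that gives any vaccines due before they are registered for cash, so coverage recorded after allocation is known would no longer be a clean baseline.

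**Analysis (Data Analysis).** Name the balancing variables as covariates in the primary models, whatever their observed association with the outcome.

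**Cost.** No extra participants. Households are to be listed anyway, and vaccination status is already on the child questionnaire. Allocation must wait for the listing and, if coverage is used, for the baseline round in all 20 camps, which may delay registration for cash. The models spend one or two of about 18 degrees of freedom.
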